### Recruitment and randomisation

Eligible women will be asked by a gynaecologist, resident, clinical midwife or research nurse to participate in the trial when they undergo a planned CS. Eligible women who are planned to undergo a vaginal delivery will also be informed about this study during pregnancy in case they need an unplanned CS. Furthermore, women during induced labour and women receiving adequate therapy for pain during labour, will be asked to participate in case a CS is needed during labour for any indication.

When the decision of a CS is made and all selection criteria are met, women will be randomly allocated to single-layer (control group) or double-layer (intervention group) closure (1:1) (see Fig. 1). Randomisation will be performed using a web-based application ALEA 2.2 which displays a computer-generated random number, managed by the Clinical Research Unit of the Amsterdam UMC - location AMC. We will use a permuted block-design, stratified for recruiting centres and for planned or unplanned CS. All women that decline to participate will be registered anonymously in order to record the number and reason for refusal. Subjects who withdraw from this study will not be replaced. 

Gynaecologists, residents, clinical midwives or research nurses enrol participants and assign them to the intervention. The CS will be performed by either a gynaecologist, a resident supervised by a gynaecologist or by a resident that is authorised to perform CSs without supervision. Participants and sonographers will be blinded for the closure technique. If operative reintervention after CS is needed and the gynaecologist that performs the reintervention needs to know the closure technique that the participant was assigned to, unblinding is possible through the logistic trial coordinator. We expect this situation to occur very infrequently.

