### Intervention (double-layer closure)

In both study arms, women will undergo a CS following a standard way with respect to mode of uterotomy, correct approximations of the cutting edges and non-closure of the peritoneum. In the intervention arm, double-layer closure of the uterus will be performed using unlocked multifilament continuous running sutures for both layers and the endometrial layer will be included in the first layer (see Fig. 2). The second layer is a continuous running suture that imbricates the first layer. Since this is not the standard method for uterine closure in the Netherlands, a short online instruction film will be shown to all participating centres and surgeons prior to participation (see Additional file 2). Surgical outcomes will be registered after the procedure in the electronic case report form (eCRF).

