### Control group (single-layer closure)

The control group will receive usual closure technique of the uterus: a single-layer closure using unlocked continuous running multifilament sutures. The currently available evidence is inconclusive with respect to endometrial saving technique or not. Therefore, we decided that in our study surgeons are free to choose to close either full thickness (including the endometrium) or split thickness (excluding the endometrium) in the control group. The applied method, including endometrial saving technique or not, will be registered.

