Within the single-layer group (control group) we will compare the primary outcome between women in whom endometrial saving technique (split thickness) was applied and women in whom an endometrial saving technique was not applied (full thickness).

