We also expect some limitations. Baseline characteristics will be collected through questionnaires that are filled in by women in the first month after CS, which might lead to recall bias regarding medical history, complications during pregnancy and labour, and other baseline measurements. We decided to lower the administrative load for participating hospitals by obtaining these characteristics through the participants. Furthermore, there is no validated questionnaire available yet for postmenstrual spotting; therefore, the questionnaires that are used in the 2Close study are not adjusted or validated for these symptoms. Moreover, the surgical techniques performed during the CS in this study are standardised in both study arms except for saving the endometrium in the control group. There is no conclusive evidence whether or not to save the endometrium in the suture according to its influence on niche development. Therefore, we chose to leave this decision with the surgeons. There may possibly be a difference in the incidence of niche development between the participants receiving single-layer split thickness or full thickness closure, also when compared to the incidence of niche development in the double-layer group. This will be further examined in a subgroup analysis.

To prevent bias regarding niche evaluation three months after CS, all ultrasonographic examiners are trained by an online learning program and a sample of ultrasounds will be evaluated. The learning module is based on the results of a Delphi procedure among international niche experts. [11] Although the niche examiners in the 2Close are trained by a standardised method, experience in measuring niches and as a consequence differences in niche measurement may occur among examiners.

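### Split- versus full-thickness closure is the surgeon's choice and occurs only among controls: the planned comparison is non-randomised with no stated adjustment, and the niche analysis announced in the Discussion is missing from the analysis section

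*Protocol article*

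**What the plan says.** *Recruitment and randomisation* allocates women 1:1 to single- or double-layer closure. On balance it says "We will use a permuted block-design, stratified for recruiting centres and for planned or unplanned CS". Endometrial technique is neither randomised nor a stratification factor.

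The two arms treat the endometrium differently. Under *Intervention (double-layer closure)*, "the endometrial layer will be included in the first layer". Under *Control group (single-layer closure)*, "surgeons are free to choose to close either full thickness (including the endometrium) or split thickness (excluding the endometrium) in the control group", and "The applied method, including endometrial saving technique or not, will be registered".

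Two places use this information:

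- *Data-analysis*: "Within the single-layer group (control group) we will compare the primary outcome between women in whom endometrial saving technique (split thickness) was applied", compared with controls in whom it was not. The outcome is spotting days and the double-layer arm is not involved.
- *Strengths and limitations*: niche incidence may differ between split- and full-thickness controls, "also when compared to the incidence of niche development in the double-layer group. This will be further examined in a subgroup analysis".

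*Data-analysis* also describes an adjusted linear regression for the primary outcome, covering the stratification factors and relevant baseline imbalances that remain despite randomisation. It is written for the comparison of the randomised groups.

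**The concern.** The arms can differ in two respects: the number of layers and whether the endometrium is sutured. The article itself raises the possibility that the second affects niche development, so readers will look to the technique comparison to help interpret the main result.

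As written, that comparison rests on a choice made by the operator. Surgeons, centres and clinical situations in which split thickness is preferred may differ in other ways that bear on spotting or niche formation. An unadjusted difference could then be read as an effect of technique when it is partly case mix or operator.

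The contrast with the double-layer arm raises a further problem. That arm has no split-thickness counterpart, so a technique-defined part of the controls would be set against an entire randomised arm. The protection of randomisation is lost, and the analysis section does not say how the contrast would be done.

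**Working it through.** **1. The plan's own figure.** Inputs from *Sample size calculation*: difference 0.5 day, SD 3.4, two-sided 5%, power 80%.

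n per arm = 2 × (1.960 + 0.842)² × 3.4² / 0.5² ≈ 726, or 1452 in total. The article states 1488, so the figure reproduces to within 2.4%. Then 1488 / 0.65 = 2289.2, rounded up to the stated 2290. This figure is not in dispute. It gives 1488 / 2 = 744 evaluable controls.

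**2. The two sections side by side.**

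| | *Data-analysis* | *Strengths and limitations* |
|---|---|---|
| Outcome | spotting days | niche incidence |
| Groups | split vs full, controls only | split vs full, and against double-layer |
| Adjustment | none stated for this comparison | none stated |

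Endometrial technique is not in the subgroup list in *Data-analysis* either. The analysis announced in the Discussion therefore has no counterpart in the analysis section.

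**3. What the within-control comparison can show.** The article gives no split-thickness share, so the share s is an assumption. With a = 744s and b = 744 − a, SE = 3.4 × √(1/a + 1/b). The smallest difference detectable with 80% power is 2.802 × SE. The last column assumes that case mix or operator alone shifts the mean by 0.25 day, with no true effect of technique.

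| Assumed share | SE (days) | Power for 0.5 day | Detectable at 80% | Chance of p < 0.05 from a 0.25-day shift |
|---|---|---|---|---|
| 10% | 0.416 | 22% | 1.16 | 9% |
| 20% | 0.312 | 36% | 0.87 | 13% |
| 30% | 0.272 | 45% | 0.76 | 15% |
| 50% | 0.249 | 52% | 0.70 | 17% |

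The power column needs only the protocol's SD and the assumed share. The last column also needs the assumed shift.

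**4. Clustering, as an illustration only.** Assume 30 equal centres, technique constant within each centre, and an intraclass correlation (ICC) of 0.01, 0.02 or 0.05. Cluster size is 744 / 30 = 24.8. The design effect 1 + 23.8 × ICC is 1.24, 1.48 or 2.19. The true size of an unadjusted 5% test, 2 × [1 − Φ(1.96 / √design effect)], is 7.8%, 10.7% or 18.5%. None of these three assumptions is in the document.

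**5. Whether a randomised contrast is available.** Centre is a stratification factor and the control technique is registered. A label attached to a whole centre applies to both of its arms, so double- versus single-layer closure within centres of one class is still a comparison by random allocation. A label attached to individual controls by the technique they received does not have this property.

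**The case against.** The case against is substantial. The article explains why the choice is free, has it registered and lists it among the limitations. It never calls the technique comparison randomised or confirmatory. Model detail for a secondary analysis is commonly left to the full protocol or analysis plan, neither of which is shown. The sentence in the Discussion is loosely worded. The stated objective compares double- with single-layer closure, so separating layers from endometrial inclusion is not a question the trial set itself.

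Most of this stands. A missing model specification alone would not be a finding. Two things remain. First, the adjusted model that the article does describe is tied to the randomised groups, while the technique comparison is stated without adjustment although it needs it more. Second, the article promises an analysis, on another outcome and with another comparator, that its analysis section does not contain. Surgeon choice is listed as a limitation, but the confounding that follows from it is not mentioned.

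A reader might also infer that centre and planned or unplanned status are known to determine the technique. No section says so; the article says only that surgeons choose. Confounding is possible by design, but its presence is not shown.

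**Conclusion.** The point holds as a correction to a secondary analysis. The split- versus full-thickness comparison is non-randomised and has no stated adjustment. The niche-incidence analysis promised in the Discussion is absent from *Data-analysis*, and in its most obvious form would not be a randomised contrast.

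Three stronger readings are not supported:

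- *That the trial's main result is compromised.* The intention-to-treat comparison of double-layer with usual single-layer closure is untouched.
- *That a randomised contrast by technique is impossible.* Only the version based on each woman's applied technique fails. Grouping by centre recovers one from data already held.
- *That the test has a false-positive rate of 8% to 19%.* This range rests on an assumed number of centres, assumed ICCs and technique constant within centre. If both techniques occur within centres, the inflation shrinks and may vanish. The 9% to 17% range likewise rests on an assumed 0.25-day shift and an assumed share.

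The size of any bias or error inflation cannot be derived from the document. On the protocol's own SD, however, power for 0.5 day is at most about 52%, so a null technique comparison would not be reassuring.

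**What to change.** 1. **Within controls.** Analyse split versus full thickness by regression adjusting for planned or unplanned CS and the collected obstetric baseline factors. Allow for centre by a fixed or random effect, or by cluster-robust standard errors where technique is nearly constant within centre. Use covariates settled before closure; blood loss and extra haemostatic sutures may follow from the technique. Report the result as observational.
2. **Against double-layer closure.** Classify each centre by the predominant technique registered for its controls, and apply the label to both arms. Compare the randomised arms within each class and test the interaction, for spotting days and for niche incidence. The within-class contrasts are randomised. A difference between classes may still reflect other differences between centres, and should be reported with that caution.
3. **Wording.** Make *Data-analysis* and *Strengths and limitations* name the same outcomes, groups and comparators.

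The cost is a little more analysis work, low power, and an approximate classification in centres that use both techniques. No new data are needed. Recording the intended control technique before randomisation would sharpen step 2 but is optional: midwives or research nurses may assign women without knowing the operator's intention, so it may not be a trivial addition.

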#### Economic evaluation

The economic evaluation will be performed alongside the RCT from a societal perspective. Both a cost-effectiveness and cost-utility analysis will be performed with a time horizon of nine months to relate the difference in societal and healthcare costs between double-layer and single-layer unlocked uterine closure during a CS to the difference in clinical effects. Healthcare costs include costs of primary and secondary care, complementary care and home care. Costs in other sectors include presence and absence from paid and unpaid work. The friction cost approach will be used to estimate indirect costs. For the valuation of health care utilization standard prices published in the Dutch Costing guidelines will be used. [34] Medication use will be valued using prices of the Royal Dutch Society for Pharmacy.

Societal costs will be related to the following effect measures in the economic evaluation: days with postmenstrual spotting and quality-adjusted life-years (QALYs) based on the Dutch tariff for the EuroQol (EQ-5D-5L). [27, 28, 35]

We hypothesise that double-layer uterine closure will reduce postmenstrual spotting and related consultations for gynaecological or fertility related problems and applied therapies, and as a consequence that it will be cost-effective in comparison with single-layer uterine closure.

The analysis will be done according to the intention to treat principle. Missing costs and effect data will be imputed using multiple imputation. Incremental cost-effectiveness ratios (ICERs) will be calculated by dividing the difference in mean total costs between the treatment groups by the difference in mean effects. Bootstrapping with 5000 replications will be used to estimate 95% CI around cost differences and the uncertainty surrounding the ICERs. Uncertainty surrounding the ICERs will be graphically presented on cost-effectiveness planes. Cost-effectiveness acceptability curves showing the probability that double-layer uterine closure is cost-effective in comparison with single-layer uterine closure for a range of different ceiling ratios will also be estimated. Adjustment for confounders and effect modifiers will be done if necessary. [36]

#### Interim analysis and safety monitoring

Because of the type of intervention, the Medical Ethics Committee (MEC) determined that the risk for participation is negligible. Therefore, we do not have a Data Safety Monitoring Committee. No interim analysis is planned.

All serious adverse events (SAEs) will be reported to the MEC by line listing yearly. Life threatening SAEs or an event that leads to death will be reported to the MEC immediately. All SAEs will be followed until they have abated, until a stable situation has been reached or the patient was discharged. We do not expect to terminate the study prematurely given the low risk of adverse events.

#### Confidentiality and data security

All participating centres receive a login name and password to gain access to ALEA 2.2, the web-secured randomisation database. Randomisation is performed pseudo-anonymously with only the initials and year of birth of the participants. Linking personal data to the study number can only be performed in the local participating centres or by the trial coordinator (SS). Written informed consent forms are stored in every centre in a lockable room. All forms and data will be archived for 15 years in the participating centres.

## Discussion

In the last years, studies examining complications of CSs are increasing, including the development of niches or thin residual myometrium at the site of the previous CS and related symptoms. Both RMT and the presence of a niche have been associated with postmenstrual spotting. [8, 10] Double-layer unlocked closure has been shown to result in a thicker residual myometrium and as a consequence can possibly lead to a decrease of niche development after a CS compared to single-layer closure. [5, 22, 24, 37] However, the long-term clinical outcomes in terms of postmenstrual spotting or subfertility have not been studied previously or have not been related to ultrasound findings. We hypothesise that niche related postmenstrual spotting and fertility problems will reduce together with decrease in niche prevalence, in which identification of the best uterine closure technique regarding RMT and niche development will be of great significance.

### Strengths and limitations

The design of this study is one of the strengths; this is the first large RCT that will evaluate the effectiveness of double-layer uterine closure compared to single-layer uterine closure after CS regarding niche related gynaecological symptoms and reproductive outcomes with a long-term follow-up. The study is adequately powered. Randomisation is performed by using a web based randomisation program. Furthermore, all participants and examiners are blinded which reduces the chance for bias regarding reported symptoms and ultrasound findings. An additional strength is the uniform manner in which we try to perform double-layer closure and ultrasound evaluation, instructed by mandatory online instruction film and e-learning, respectively. Moreover, the 2Close study will compare the cost-effectiveness of both techniques which has never been done before. As we expect that double-layer closure will reduce the incidence of niche development and as a consequence that it could possibly reduce the gynaecological symptoms including postmenstrual spotting after CS, we assume double-layer closure to be more cost-effective. Also, we expect that double-layer closure will improve the chances of conceiving after CS and lower costs in fertility treatment.

We also expect some limitations. Baseline characteristics will be collected through questionnaires that are filled in by women in the first month after CS, which might lead to recall bias regarding medical history, complications during pregnancy and labour, and other baseline measurements. We decided to lower the administrative load for participating hospitals by obtaining these characteristics through the participants. Furthermore, there is no validated questionnaire available yet for postmenstrual spotting; therefore, the questionnaires that are used in the 2Close study are not adjusted or validated for these symptoms. Moreover, the surgical techniques performed during the CS in this study are standardised in both study arms except for saving the endometrium in the control group. There is no conclusive evidence whether or not to save the endometrium in the suture according to its influence on niche development. Therefore, we chose to leave this decision with the surgeons. There may possibly be a difference in the incidence of niche development between the participants receiving single-layer split thickness or full thickness closure, also when compared to the incidence of niche development in the double-layer group. This will be further examined in a subgroup analysis.

To prevent bias regarding niche evaluation three months after CS, all ultrasonographic examiners are trained by an online learning program and a sample of ultrasounds will be evaluated. The learning module is based on the results of a Delphi procedure among international niche experts. [11] Although the niche examiners in the 2Close are trained by a standardised method, experience in measuring niches and as a consequence differences in niche measurement may occur among examiners.

### Potential impact and implications

This study will gain insight in the most optimal uterine closure technique after CS which is relevant for women and gynaecologists, since we will focus on long-term gynaecological symptoms and reproductive outcomes in relation to changes of the lower uterine segment after CS and in particular niche development. Since many studies have already shown that RMT and niches are related to several symptoms and therapies for niche resection are being developed, we think it is necessary to provide evidence for the development of preventive strategies regarding niche related symptoms. It is important to realise that the best way to prevent a niche and its related symptoms, is to not perform a CS. But since it is often inevitable to perform a CS, care takers should perform it in the most optimal way.

After the results of this study become available, the most optimal and cost-effective technique can be implemented in order to reduce symptoms and problems in a subsequent pregnancy. This will not be difficult, since the technique is easy to learn and many gynaecologists and residents are familiar with it after the trial. Especially for a scheduled CS, women should be informed about the risk to develop a niche and the risk that it might cause symptoms or complications later in life.

## Abbreviations

AMT: Adjacent myometrium thickness
BROK: Basic course Regulations and Organisation for Clinical researchers
CI: Confidence interval
eCRF: electronic case report form
CS: Caesarean section
GCP: Good clinical practice
GIS: Gel instillation sonohysterography
ICER: Incremental cost-effectiveness ratio
iMCQ: iMTA Medical Consumption Questionnaire
iMTA: Institute for Medical Technology Assessment
iPCQ: iMTA Productivity Cost Questionnaire
IQR: Interquartile range
MEC: Medical ethics committee
OR: Odds ratio
QALY: Quality adjusted life years
QOL: Quality of life
RCT: Randomised controlled trial
RMT: Residual myometrium thickness
RR: Relative risk
SAE: Serious adverse event
SD: Standard deviation
SIS: Saline infusion sonohysterography
TVUS: Transvaginal ultrasound
VAS: Visual analogue scale
